### Ethics approval

The study received the Institutional Ethics Committee (IEC) approval on September 15, 2021: Rajagiri Institutional Ethics Committee. Ref No: RCSS/IEC/009/2021. All study participants and one of the participating family members will provide written consent to participate. Further participants will be informed about confidentiality, the voluntary nature of participation and their right to withdraw from participation at any point of study.

### Study procedure

The initial phase would focus on developing a collaborative family approach within the unique cultural milieu of Kerala, India, to maximize acceptability. The team will perform the forward/back-translation of standardized scales and indexes into the local language (Malayalam). This phase would also involve the development of an accompanying fidelity scale to guide and test the implementation of the ABFT model in the selected population so that mediators for good outcomes could be evaluated. Social Work Trainees (SWTs) supervised by the professional mental health team consisting of a psychiatrist, clinical psychologist, psychiatric social workers and psychiatric nurses would assess and provide intervention. The mental health team has supervisory, trouble-shooting, and evaluative functions. Social worker trainees would record qualitative observations regarding processes and outcomes to complement the measurement tools to enhance the overall evaluation. Focus group discussions would also be employed to review progress and address any treatment issues. The feasibility trial phase would last up to 6 months until SWTs demonstrated reasonable competence in the use of measurement tools and the intervention packages. The last phase will involve a cluster-randomized trial with a targeted sample size of 158 people who has SHB presenting at emergency departments at selected clusters in Kerala. The ABFT model will be implemented bi-weekly for 6 months, and the results will be compared with a treatment-as-usual (TAU) comparison group (medical management).

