### Study setting

A list of NABH (National Accreditation Board for Hospitals and Healthcare) Accredited hospitals from Kerala state, India, will be prepared to select the intervention clusters. The inclusion criteria for selecting hospitals will be any NABH accredited Tertiary referral multi-speciality hospital with a minimum of 500 inpatient beds. Eligible hospitals will be randomized to intervention or control groups in a 1:1 allocation ratio. We will sign a referral agreement with the emergency department in charge and their team after explaining to them the purpose. Emergency departments of the chosen hospitals will be considered as individual clusters, and all those who presented to the emergency departments of these hospitals after serious suicidal attempts will be assessed by the professional social workers working in the department. The Social Workers will induct the people and their family members after educating them about the purpose of the study and getting informed consent. The consented people from the experimental cluster will receive the treatment as usual (TAU) plus FASE intervention, and the people belongs the control clusters will receive the treatment as usual (TAU) interventions. The stages of enrolment, intervention, and assessment can be seen in Figure 1.

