### Statistical analysis plan

#### Sample size and power calculation

A sample size of 282 will be collected from 10 clusters, with an average of 28 required from each of the 10 clusters. The clusters receiving the FASE intervention and the clusters receiving the usual care will be randomized 1:1 ratio and 28 samples will be recruited for the study allowing for a 20 % loss in follow-up rate. The Critical z is 1.64 and *R*^2^ is 0.3 with 95% power, a two-sided alpha of 5% with a cluster effect of 0.05 results in a sample size of 256. The 95% power and additional 10% respondents would allow us to maintain at least the 80% power even after the 20% loss to follow-up. Thus, we aim to recruit 282 participants for this study.

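### The protocol states two recruitment targets for the same cluster trial, 158 and 282; nothing derives 158, and the power statement does not cover it

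*Protocol article*

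**What the plan says.** Two sections of the protocol article set a target for the cluster-randomised phase.

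- **Study procedure:** "The last phase will involve a cluster-randomized trial with a targeted sample size of 158 people". This follows directly after the description of the feasibility phase, and it names the last phase and the cluster-randomised design.
- **Sample size and power calculation** opens with a different figure: "A sample size of 282 will be collected from 10 clusters, with an average of 28 required from each of the 10 clusters". It concludes: "Thus, we aim to recruit 282 participants for this study".

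The second section gives some basis for its figure. The calculation, "with 95% power, a two-sided alpha of 5% with a cluster effect of 0.05 results in a sample size of 256", uses a critical z of 1.64 and an R² of 0.3. The increase from 256 to 282 is then justified by: "The 95% power and additional 10% respondents would allow us to maintain at least the 80% power even after the 20% loss to follow-up".

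Trial design confirms that Phase 2 is a pre-post study in one hospital and that only Phase 3 is cluster-randomised. Study setting gives the allocation: "Eligible hospitals will be randomized to intervention or control groups in a 1:1 allocation ratio".

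**The concern.** The recruitment target decides when enrolment ends, and here one trial has two targets that differ by 124 people. The power statement (95%, and at least 80% after 20% loss) is attached to 256 and 282 only. A team that stopped at 158 could point to Study procedure as its authority, and a reader of the results could not tell whether the trial had finished or had stopped short. While both figures stand, the choice between them also remains open after data have begun to accrue.

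**Working it through.** **1. Reproduce the plan's figure.** 256 × 1.10 = 281.6, rounded up to 282; 282 / 10 = 28.2 per cluster. Both steps agree with the text. The base of 256 cannot be recomputed, because no effect size (mean difference and SD, odds ratio or similar) is stated.

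**2. Look for an origin of 158.**

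| Candidate | Value |
|---|---|
| Calculated size before the added 10% | 256 |
| One arm of 282 | 282 / 2 = 141 |
| 282 after 20% loss | 282 × 0.8 = 225.6, about 226 |
| 158 read as one arm | 2 × 158 = 316 in total |

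None links 158 to 282. The feasibility phase is ruled out because Study procedure assigns 158 to the last phase.

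**3. Size of the gap.** (282 − 158) / 282 = 124 / 282 = 44.0%. Against 256: 98 / 256 = 38.3%. If 158 also came from 10 clusters, which Study procedure does not say, it would be 15.8 per cluster against 28.2.

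**4. Power, as a range.** Assumptions: 10 clusters; the cluster effect of 0.05 is the intracluster correlation and is already allowed for in 256; 256 gives 95% power; the final test is two-sided at 5%.

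- Design effect: DE(N) = 1 + (N/10 − 1) × 0.05.
- Effective size: N / DE(N).
- Noncentrality: λ(N) = λ₀ × √{[N/DE(N)] / [256/DE(256)]}, with 256 / 2.23 = 114.8.
- λ₀ has two possible values, because the section pairs a critical z of 1.64 (the one-sided 5% value) with a two-sided alpha (z = 1.96). If 256 was calculated with 1.64, λ₀ = 1.645 + 1.645 = 3.29. If with 1.96, λ₀ = 1.960 + 1.645 = 3.60.
- Normal power is Φ(λ − 1.96). The t version uses a noncentral t on 10 − 2 = 8 df.

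| Analysed N | DE | N/DE | λ (z 1.64 / 1.96) | Normal power | t (8 df) power |
|---|---|---|---|---|---|
| 282 | 2.36 | 119.5 | 3.36 / 3.68 | 92% / 96% | 84% / 89% |
| 225.6 (282 less 20%) | 2.08 | 108.6 | 3.20 / 3.51 | 89% / 94% | 80% / 87% |
| 158 | 1.74 | 90.8 | 2.93 / 3.21 | 83% / 89% | 73% / 80% |
| 126.4 (158 less 20%) | 1.58 | 79.9 | 2.74 / 3.01 | 78% / 85% | 67% / 75% |

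Like for like after 20% loss, 158 in place of 282 costs about 9 to 11 percentage points on the normal approximation and about 12 to 13 on the t.

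**The case against.** The strongest reply is that the sample-size section is the dedicated one. It states 282 twice, shows the step from 256 and repeats the cluster size, so a careful reader would take it as controlling and 158 as leftover text. That is plausible, and it means that stopping at 158 is a possibility and not a prediction. It does not remove the contradiction: both figures stand as current text, and nothing says which one governs. Nor is this a matter of journal condensation, since the article gives two incompatible values and has not merely left one out.

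A second reply concerns power, and it largely stands. A reader might infer that a trial of 158 must fall below the promised 80% after loss. The document does not support that. If 256 was calculated with a two-sided z of 1.96, the normal approximation leaves 85% with 126 analysed. The 78% arises only if 256 was calculated with the one-sided 1.64 and the test is then two-sided, which brings in a separate inconsistency of the sample-size section. The t figures add another separate matter, the small number of clusters: with the 1.64 calibration, the t version gives only 82% at 256 itself. All these figures also assume 10 clusters for the 158, a number that Study procedure does not give.

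A third inference would be that 282 is therefore the right number. That goes too far as well, because 282 rests on a 256 that has no stated effect size and on a critical value that does not match the stated alpha.

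**Conclusion.** The point holds as an internal contradiction in a basic design figure. The same cluster trial has targets of 158 and 282. The smaller is 44% below the larger and 38% below the 256 tied to 95% power, and it has no derivation. This conclusion needs no assumption.

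The effect on power does. Under the conditions set out above, 158 less 20% loss gives about 78% to 85% (normal) or 67% to 75% (t, 8 df). The lower end of each range takes 256 as calculated with z = 1.64, the upper end with z = 1.96. The supportable statement is that the published power claim does not cover a trial of 158, and that the promised 80% after loss may not be met. It cannot be said that it will certainly be missed. It needs correcting because the target is a figure the trial relies on and the correction is cheap.

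**What to change.** Delete 158 from Study procedure and reconcile that section with Sample size and power calculation, so that one recruitment target appears with its derivation. On the current text only 282 (about 28 in each of 10 clusters) has any derivation. Confirm or replace it when the critical z and the two-sided alpha are brought into agreement and the assumed effect size is stated; do not carry it over unchecked. Use the resulting figure throughout, and check that the registry entry and ethics documents, which are not visible here, carry the same one.

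The cost is a one-line edit in Study procedure, a recalculation that the sample-size section needs in any case, and a check of the related documents. It should be done before enrolment reaches 158, so that the stopping point is not chosen once that number has been recruited.

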### Outcome

Study outcomes are assessed at baseline and 6-month follow-up. Demographic characteristics measured at baseline include age, gender, marital status, education, occupation, and family income. The following information on the clusters selected will be collected: number of hospital beds, patients, social workers, primary treatment modalities, and the average length of stay at the hospital. Measurement domains and time points are summarized in Table 1.

**Table 1 T1:** Measurement domains and data collection time points.

**Variable**	**Dimensions included**	**Measurement tool**	**Data collection time points**		
			**Baseline (T0)**	**3 months (T1)**	**6 months (T2)**
Demographic assessment	Age, sex, marital status, education, occupation, and family income		✓		
Suicidality	Suicidal thoughts and ideation	Depressive Symptom Inventory–Suicidality Subscale (DSI-SS)	✓	✓	✓
Depression, anxiety, stress	Depression, anxiety, stress	DASS 21	✓	✓	✓
Social support	Emotional support, tangible support, affectionate support, positive social interaction	The MOS social support survey	✓		✓
Resilience	Resilience	The Brief Resilience Scale (BRS)	✓		✓
Customer satisfaction		Questionnaire			✓

#### Primary outcome

The primary outcome will be the total suicidality score measured by the Depressive Symptom Inventory–Suicidality Subscale (DSI-SS) (21). The DSI-SS is a 4-item self-report questionnaire designed to assess the frequency and intensity of suicidal ideation and impulses in the past 2 weeks. The scale measured suicidality on a four-point scale ranging from 0 to 3, with higher scores indicating greater severity of suicidal ideation. DSI-SS scores exhibited good internal consistency, ω = 0.90 [95% CI =0.89–0.91], convergent validity (rs = 0.52–0.74), discriminant validity (rs = 0.12–0.27) (22).

#### Secondary outcome

Secondary outcomes to be measured include depression, anxiety, mental well-being, social support, resilience, customer satisfaction, and appropriate use of primary care and community resources.

##### Depression, anxiety, stress

DASS 21 is a shortened version of Depression, Anxiety and stress scale developed by Lovibond and Lovibond (23). Participants will be asked to rate their levels of depression, anxiety and stress on a 4-point severity/frequency scales over the past week. Subscales include seven questions each which is computed to obtain total scores for depression, anxiety and stress. Higher scores on the scale indicate high severity of symptoms. The DASS 21 tool exhibits high internal consistency, with alpha coefficients of 0.85, 0.81, 0.81 respectively for depression, anxiety and stress scales and is a tested valid in Indian population (24). The study will look for a decrease in depression scores from baseline to follow-up among participants in both groups to test the effectiveness of the intervention.

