## Materials and methods

### Aim of the study

The research has two aims, to build evidence on the effectiveness of an Attachment-Based Family Therapy and Resource linkage model to prevent suicide in people presenting with self-harm behaviors in emergency departments at tertiary hospitals in Kerala; Secondly, to evaluate the efficacy of the process of delivery of services and assess the cost-effectiveness of sharing the care task with the social work trainees supervised by the mental health team, through a continuum of care from critical health care to family-based services. The research team has been developing this model for over the past 2 years. The results of this feasibility trial would provide insights into the model's effectiveness in responding to multiple and complex psychological and social precipitants to deliberate self-harm that are currently ignored in general health services.

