### Objectives of the study

The major objectives of the study include

Evaluate the contribution of psychosocial factors to self-harm behavior and the role of psychosocial aspects in preventing suicide.Develop the ABFT and Community Linkage model for the prevention of suicide in a group of people presenting with self-harm behavior at emergency departments;Compare the treatment (TAU) as the usual plus FASE intervention with the TAU using a cluster RCT design framework;Develop the systems and processes appropriate to deliver the services for people presenting with self-harm behavior at emergency to integrate a psychosocial intervention that would have broad relevance and application nationally and in low and middle-income countries;Assess the proposed model's cost-effectiveness for managing self-harm behavior focused on a seamless continuum of care from acute health to community services.

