### Trial design

The study involves three phases;

Phase 1: development of a family-based intervention with the three components, Comprehensive psychosocial assessment and assertive engagement, Attachment-Based Family Therapy (ABFT), and community resource linkages.Phase 2: the feasibility trial of the developed intervention, andPhase 3: the cluster randomized control trial of suicide prevention intervention among randomly selected tertiary hospitals in Kerala.

In phase one, the development of intervention components includes a need assessment survey followed by a rapid systematic review of the preventive interventions for suicide and self-harm. A qualitative and quantitative need assessment was conducted among 44 patients who presented with self-harm behaviors in a tertiary hospital in Kerala between October and December 2020 (results submitted elsewhere). The rapid systematic review and the assessment findings guided the components of the intervention. In the second phase, the developed intervention will be tested for feasibility and effectiveness in a tertiary hospital in Kerala using a pre-post interventional design. Phase three comprises the experimental trial of the finalized care package using a cluster-randomized trial in different tertiary hospitals in Kerala.

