### Participant recruitment

A feasibility trial will be performed in one of the clusters among patients presenting with self-harm behaviors at their emergency department. Social workers under the supervision of the head of the department of critical care and emergencies in the hospital and the project lead will form a multidisciplinary team to run the project. Professional social workers employed in the hospital are responsible for recruitment, baseline and follow-up assessments, and initial interventions. The mental health team will confirm the caseness of each potential participant after scrutiny of the filled-up assessment framework. The disagreements, if any, will be sorted out by the confirmatory assessment by the mental health team. As part of their field placement, a pool of social work trainees from the social work institutions across the State will deliver the follow-up telephonic interventions. Baseline and 6-month follow-up assessments will be performed using a set of standardized questionnaires. After completing the 6-month-long feasibility trial, the intervention will be tested in the emergency departments of randomly selected clusters.

Criteria for the participants of the cluster-randomized trial include:

The participants should fulfill the standard definition of suicide attempt: “An act with a non-fatal outcome, in which an individual deliberately initiates a non-habitual behavior that without intervention from others will cause self-harm, or deliberately ingests a substance above the prescribed or generally recognized therapeutic dosage, and which is aimed at realizing changes which the subject desired *via* the actual or expected physical consequences” (18).

Inclusion criteria is as follows:

Patients presenting with attempted suicide or self-harm behaviors at emergency departments of the selected hospitals will be included.We will include patients with age over 18 with non-habitual deliberate self-harm, and serious suicide attempts admitted to the emergency section or emergency rooms within 14 days of their index attempt to get treated for their physical issues.We will include the patients with chronic medical conditions (especially dreadful diseases), in the study, assuming that despite their constant contact with the medical facility and frequent hospital admissions due to their physical conditions, the system insensitivity could result in patients slipping through the mental health or suicidal ideation detection gateways.

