#### Data analysis

Hard copies of data will be stored in a secure place, while soft data will be stored securely using file locks and passwords. Basic descriptive statistics will be computed for outcomes. The main effects of the interventions will be assessed on primary and secondary outcomes at different time points before and after the intervention. With the SPSS and R software, we will run the multiple regression modeling to determine the overall fit of the model and the relative contribution of each of the predictors to this variance. Multinomial Logistic Regression will be applied to study the exposure variables that are likely to contribute to the variation on the outcome variables, and discriminant analysis will be used to determine whether the clusters differ with regard to the predictors.

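### The effectiveness test for DASS-21 depression is worded as a fall from baseline in both groups, and an uncontrolled Phase 2 is said to test effectiveness; neither can isolate a treatment effect

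*Protocol article*

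**What the plan says.** In the subsection on depression, anxiety and stress (under Secondary outcome), the plan is to "look for a decrease in depression scores from baseline to follow-up among participants in both groups to test the effectiveness of the intervention".

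The Trial design section says that in Phase 2 the intervention will be "tested for feasibility and effectiveness in a tertiary hospital in Kerala using a pre-post interventional design". The Aim of the study section adds: "The results of this feasibility trial would provide insights into the model's effectiveness".

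Other parts of the article set out a controlled comparison. The third objective is to "Compare the treatment (TAU) as the usual plus FASE intervention with the TAU using a cluster RCT design framework". Study setting randomises hospitals 1:1. Study procedure says the results will be set against a TAU group. The Control group section applies the same measurement tools to both groups.

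On timing, the inclusion criteria take patients "admitted to the emergency section or emergency rooms within 14 days of their index attempt", and DASS-21 asks about the past week.

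**The concern.** The sentence on depression names the result that is to test the intervention, and that result is a change within groups. Baseline is taken in or soon after a crisis. A lower depression score six months later is plausible in both arms whether or not FASE does anything, because people recover and because extreme scores tend to regress.

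Read literally, the criterion points the wrong way twice. Equal falls in both arms, which is what no effect looks like, would satisfy it. A fall under FASE with no change under TAU, which is what an effect looks like, would not.

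Phase 2 has a related problem. One hospital measured before and after, without a control group, cannot separate the intervention from recovery, yet the article says it tests effectiveness.

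At stake is a claim of benefit on depression, or from Phase 2, that the design cannot support, in a trial that the abstract expects to affect policy and clinical guidelines.

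**Working it through.** **Setting the passages side by side.** The objectives and Study procedure call for FASE plus TAU against TAU. The depression sentence calls for a fall in both groups. These are different estimands, and only the first uses the randomisation. The two statements must be reconciled.

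**Inputs from the article.** 282 participants, 10 hospitals, 1:1 allocation, 20% loss to follow-up and a cluster effect of 0.05, read here as the ICC. The total follows from the article's own steps: 256 × 1.10 = 281.6, rounded to 282, and 282 / 10 = 28.2 per hospital. The 256 cannot be rebuilt because no effect size is given, but nothing here depends on it. Study procedure gives a target of 158. I use 282, from the sample size section; a smaller trial would lower the within-arm probabilities below.

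**Assumptions not in the article.** No treatment effect; the same natural improvement in both arms; a baseline-to-follow-up correlation ρ of 0.5, varied from 0.3 to 0.7; and a "fall" taken as a decrease significant at two-sided 5%. The article sets no significance threshold. If any lower mean counted, the criterion would be met more often than shown.

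**Step 1: independent patients.**
- Completers per arm: 282 × 0.8 / 2 = 112.8, about 113.
- SD of change = SD × √(2(1 − ρ)), which equals 1 SD at ρ = 0.5.
- At 0.3 SD improvement: 0.3 × √113 = 3.19, and Φ(3.19 − 1.96) = 0.89. The noncentral t gives 0.885 for one arm and 0.885² = 0.78 for both.
- At 0.5 SD: 0.5 × √113 = 5.3, and the probability exceeds 0.99.
- Over ρ = 0.3 to 0.7, the probability that both arms fall is 18% to 60% at 0.2 SD, 58% to 97% at 0.3 SD, and about 99% or more at 0.5 SD.

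**Step 2: with clustering.** Simulation of 5 against 5 hospitals with 23 completers each (28.2 × 0.8 = 22.6), ICC 0.05, ρ = 0.5 and 4,000 runs. The within-arm test is a paired t-test on patients. The between-arm test is a t-test on hospital mean changes.

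| Natural improvement, both arms | Significant fall, FASE arm | Significant fall, both arms | Between-arm test rejects |
|---|---|---|---|
| 0 | 8% | 0.75% | 5.0% |
| 0.2 SD | 55% | 29% | 4.8% |
| 0.3 SD | 81% | 66% | 4.6% |
| 0.5 SD | 99% | 98% | 4.7% |
| 0.8 SD | 100% | 100% | 5.3% |

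Simulation error is at most √(0.25 / 4000) = 0.8 percentage points. The "both arms" column matches the quoted wording. The between-arm column stays at the nominal 5% because a shared improvement cancels.

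**Step 3: are such improvements plausible?** If patients enter 1 SD above their usual level, regression to the mean alone gives an expected fall of 1 − ρ, which is 0.3 to 0.7 SD for ρ of 0.7 to 0.3. The entry level is itself an assumption.

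**Phase 2** needs no arithmetic: with no control group there is no between-arm contrast to compute.

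**The case against.** The strongest reply is that this is one loosely worded sentence about a secondary outcome. It sets no threshold and names no test. Read with the objectives and Study procedure, it may only mean that change is measured in both arms and then compared, with the exact contrast left to a fuller plan. That reading is possible, and it is why this is a point of correction and not a fatal flaw. It does not remove the point: the sentence positively states what is to test effectiveness, and what it states is wrong.

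A reader might infer more, and the article does not support it:
- *That the trial discards its randomised comparison.* It does not. The objectives, Study setting and Study procedure all keep it.
- *That the primary outcome is judged in the same way.* No such criterion is stated for the DSI-SS, social support or resilience.
- *That the Data analysis section repeats the rule.* It says: "The main effects of the interventions will be assessed on primary and secondary outcomes at different time points before and after the intervention". There the before-and-after phrase describes the time points. It sets no within-group criterion.
- *That a false positive is near-certain.* That holds only at about 0.5 SD natural improvement or more. At 0.2 SD, both arms fall significantly in about 29% of trials.
- *That Phase 3 depends on a pre-post effect from Phase 2.* The article states no such progression rule, and the Aim section speaks only of insights. The Trial design section nevertheless calls Phase 2 a test of effectiveness, and that wording is unsupported.

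**Conclusion.** Wrong as written, within a limited scope. The stated test for DASS-21 depression conflicts with the article's own randomised comparison and cannot separate a treatment effect from natural recovery or regression to the mean. With no treatment effect, it would be met in about 29%, 66% and 98% of trials at 0.2, 0.3 and 0.5 SD of common improvement, against about 5% for a between-arm test on cluster means. Those figures rest on an assumed improvement, a correlation of 0.5, the ICC of 0.05 and a 5% significance threshold. The logical point needs none of them. The claim that Phase 2 tests effectiveness fails for the same reason. The randomised design and the primary outcome are not impugned.

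**What to change.** 1. Replace the sentence in the depression, anxiety and stress subsection with wording such as: *The effect of FASE on depression is the difference between arms in DASS-21 depression score at 6 months, adjusted for baseline and allowing for clustering by hospital.*
2. State that within-arm falls will be reported descriptively and not used as evidence of effectiveness.
3. In Aim of the study and Trial design, limit Phase 2 to feasibility aims such as acceptability, fidelity, recruitment and retention, and remove the claim that it tests effectiveness.

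No extra data are needed: Table 1 schedules DASS-21 at baseline, 3 and 6 months, and both arms use the same tools. Items 2 and 3 are wording only. Item 1 is also a small analysis addition, because the Data analysis section names no clustered model. With 10 hospitals the method should suit few clusters, for example an analysis of hospital-level summaries with 5 + 5 − 2 = 8 degrees of freedom, or fewer if hospital-level covariates are added.
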